Oculomotor dysfunction commonly occurs following SRC.^19^ This can manifest through symptoms of blurred vision and sensitivity to light. Abnormalities have been observed in the pupillary light reflex (PLR) following concussion.^25^ PLR is underpinned by a complex autonomic function, where pupillary constriction is dominated by the parasympathetic pathway, and dilation dominated by the sympathetic system. Traditionally, PLR was examined subjectively using a penlight test, where the practitioner shines a light into a patient’s eyes; but this lacks diagnostic accuracy and results can be confounded by changes in attention, accommodation and environmental ambient light. Pupillometry is a diagnostic technology offering a standardised and objective evaluation of the PLR, providing a quick, accurate and quantifiable evaluation of the PLR^25^ and capturing a range of outcome parameters across different phases of PLR response (eg, peak and average dilatation/constriction velocity). Normative PLR values are documented in adults, but these are affected by age,^26^ and initial data suggest that adolescents (aged 12–18 years), and particularly males, show greater maximal pupil diameters, slower maximum constriction velocities and lower percent constriction.^26^ These developmental differences make translating the results of adult studies to children difficult. Recently, PLR technology has been able to accurately display meaningful differences between adolescent athletes with a concussion and those without on eight out of nine PLR metrics,^25^ but no longitudinal data have been reported.

Evidence suggests that maladaptive coping strategies such as fear-avoidance behaviours relating to an injury have also emerged as potentially important prognostic factors in predicting prolonged recovery.^27^ Fear-avoidance behaviours have increased in relevancy to concussion recovery in adolescents.^28 29^ It would be plausible fear-avoidance and anxiety behaviours around potential or perceived injuries could be associated with prolonged symptoms. Recent studies have highlighted fear-avoidance behaviours were positively correlated with somatic symptoms, emotional distress and negatively associated with quality of life in a study involving adolescent subjects with concussion,^30^ which supports findings from adult samples.^28 29^ There is a need to explore fear-avoidance behaviours, anxiety and depressive symptoms further in the recovery from SRC in adolescents.

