### Statistical analysis

All data will be analysed using the Statistical Package of Social Sciences (SPSS) (V.26; SPSS).

Baseline outcomes (concussion history, Y Balance, PLRM) will be summarised using means and SDs for scale variables and frequencies and percentages for nominal variables. We will use histograms to examine the frequency distributions of scale variables, and where normality is assumed, we will use independent t-tests to compare baseline data (PCSS, Y Balance, PLRM), with players categorised into two groups based on self-reported history of concussion in the last 12 months (no concussion in the last 12 months or concussion within the last 12 months). To avoid bias, researchers will be blinded to group title (ie, history of concussion vs no history of concussion). The threshold for statistical significance will p<0.01 for all tests. We will also present mean differences (95% CIs) between groups for scale outcome data.

SRCs occurring throughout the 2022/23 playing season will be summarised using counts (n, %). Time to SRC event will be plotted using survival curves, with participants censored at the end of the playing season. Serial outcome data (PCSS, Y Balance, PLRM, PFAB-TBI) will be measured at 72 hours, 7 days, 14 days, 23 days, 90 days, 180 days and 365 days postconcussion; we will initially determine the number (%) of participants that had returned to baseline at each time point. We will also examine the growth/response curves for each participant, as well as compare curves between known groups; sex and concussion history. As the shape of the time-response curve is uncertain and may vary across each outcome variable, we will calculate summary measures for each participant based on either the peak value, the time to return to baseline or the area under the curve. Area under the curve will be calculated using the trapezium rule (by adding the areas under the graph between each pair of consecutive observations). The most suitable summary measure will be used in the calculation of a median score (IQRs) for each outcome variable. Between-group comparisons will also be made, comparing curves across two known groups, for example, males/females and history of concussion/no history.

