### Sample size

We aim to enrol 250 participants at baseline. This figure allows for a 20% loss to follow-up over the entire study and assumes a 10% concussion prevalence over a single playing season. This will generate recovery data from approximately 20 participants presenting with a new concussion. Recruitment will be stratified to include equal numbers of male and female participants (n=125 males; n=125 females).

A sample of 250 participants would also provide sufficient power for detecting baseline difference in sensorimotor function. Our previous research^24^ had a medium effect standardised mean difference (SMD) 0.5 between adolescents with a history of concussion to those with no history for sensorimotor function with SDs of 0.22 units (SEn). Based on an alpha level of 1%, n=180 participants would provide 90% power for detecting a medium effect difference in SEn between groups at baseline.

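### As written, the peak and AUC summaries are not referenced to preseason values, so a pre-injury difference between groups can be read as a difference in recovery

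*Protocol article*

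**What the plan says.** The Statistical analysis section lists serial outcomes at "72 hours, 7 days, 14 days, 23 days, 90 days, 180 days and 365 days postconcussion". Because the shape of the curves is not known in advance, it will "calculate summary measures for each participant based on either the peak value, the time to return to baseline or the area under the curve", and the most suitable of the three will be reported as a median with IQR. It specifies the AUC: "Area under the curve will be calculated using the trapezium rule (by adding the areas under the graph between each pair of consecutive observations". No baseline subtraction or baseline adjustment is stated for the AUC or the peak. The paragraph ends: "Between-group comparisons will also be made, comparing curves across two known groups, for example, males/females and history of concussion/no history".

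The article also gives reasons to expect these groups to differ before any new injury. The Sample size section says that earlier work "had a medium effect standardised mean difference (SMD) 0.5 between adolescents with a history of concussion to those with no history", with an SD of 0.22 SEn units. The Introduction describes the history group in that work as having the poorer balance (higher SEn). It also says that adolescents, and "particularly males, show greater maximal pupil diameters, slower maximum constriction velocities and lower percent constriction". Examining the effect of history, sex and age on these outcomes is the first objective under Aims.

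Elsewhere, recovery is referenced to baseline. The share of players back at baseline is reported at each visit, full recovery for the logistic models is a return to preseason values, and change scores are planned for the PFAB-TBI.

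**The concern.** The Discussion states the primary aim as recovery and whether history, sex and age affect it. A peak or an AUC of observed values measures the level at which a player sits plus whatever the injury added. If two groups start at different levels and recover in exactly the same way, their peaks and AUCs still differ by the starting gap. For SEn by concussion history the gap runs towards the history group looking worse, which is easily taken for slower or poorer recovery.

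The AUC is especially exposed. Its window runs to day 365, and (365 − 23)/362 = 94% of it lies after day 23, when the injury effect may be small and habitual level dominates. The preseason values that would remove the problem are already collected, but only one of the three candidate summaries uses them.

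**Working it through.** **Inputs from the article.** SMD 0.5 and SD 0.22 for SEn by history; 250 enrolled, 20% loss and 10% concussion (Sample size); visits at days 3, 7, 14, 23, 90, 180 and 365; threshold p<0.01 (Statistical analysis).

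**Assumptions not in the article.** Within-player correlation ρ between visits of 0.7, varied as shown; normal data; a Mann-Whitney comparison; the group splits shown; an injury effect of 1 SD decaying with a 14-day constant; the pre-injury gap from the earlier study holding among the players who become concussed.

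**1. The plan's own figure.** 250 × (1 − 0.20) × 0.10 = 20 concussed players. This reproduces.

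**2. Offset carried by each summary when recovery is identical.** Gap = 0.5 × 0.22 = 0.11 SEn units at every visit.
- Peak: shifted by 0.11.
- AUC: 0.11 × (365 − 3) = 0.11 × 362 = 39.8 unit-days.
- The same constant passes into group medians.
- In SD units the AUC offset is 0.5 × 362 = 181 SD-days. The assumed injury effect itself contributes only about 15 SD-days.
- The visit schedule under Outcome measures has day 21 instead of day 23. The span is still 362 days, so the 39.8 does not change.

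**3. Standardised size for the AUC.** Trapezium weights are 2, 5.5, 8, 38, 78.5, 137.5 and 92.5 days (sum 362). The sum of squared proportional weights is 35,167/362² = 0.268. In SD units:
- variance of AUC as written = ρ + (1 − ρ) × 0.268
- variance of baseline-subtracted AUC = (1 − ρ) × 1.268

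| ρ | SD as written | SD of change | Standardised gap as written (0.5/SD) | SD reduction |
|---|---|---|---|---|
| 0.6 | 0.841 | 0.712 | 0.59 | 15% |
| 0.7 | 0.883 | 0.617 | 0.57 | 30% |
| 0.8 | 0.924 | 0.504 | 0.54 | 45% |

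The two variances are equal when ρ = 1 − ρ, that is at ρ = 0.5. Below that, subtraction still removes the offset but costs precision.

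**4. False positives at p<0.01.** Simulation of 10,000 trials per setting, with identical recovery and a pre-injury SMD of 0.5:

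| Split | ρ | Peak as written | AUC as written | Peak change | AUC change |
|---|---|---|---|---|---|
| 10 v 10 | 0.5 | 5.9% | 7.2% | 0.8% | 0.7% |
| 10 v 10 | 0.7 | 5.0% | 5.4% | 0.7% | 0.8% |
| 10 v 10 | 0.9 | 4.2% | 4.7% | 0.7% | 0.7% |
| 5 v 15 | 0.5 | 3.3% | 4.2% | 0.6% | 0.7% |
| 5 v 15 | 0.7 | 2.9% | 3.0% | 0.4% | 0.4% |
| 5 v 15 | 0.9 | 2.8% | 3.1% | 0.5% | 0.6% |

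The mean group difference was about 0.50 SD for both measures as written, and about 0.00 SD after baseline subtraction.

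**The case against.** **The article never says that baseline is not subtracted.** The trapezium rule works equally well on a graph of changes, and an analysis plan that is not shown could specify this. That stands as a limit on certainty. Still, the AUC is given as a formula on consecutive observations from a list of post-injury visits, and the candidate beside it is explicitly tied to baseline. Observed values are the natural reading.

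**Baseline is already central to the recovery analysis.** This also stands. The return-to-baseline counts and the logistic models of age, sex and previous injury are baseline-referenced, and PFAB-TBI has change scores. The history gap in Y Balance outcomes will be visible in the baseline table. A reader might infer that the plan ignores preseason values throughout; it does not. None of these provisions, however, is linked to the peak, the AUC or the curve comparison.

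**The error rates rest on an unnamed test.** The plan says only that curves will be compared, and the correlation and group splits are assumed. Rates at a 5% level would look more alarming but do not apply, since the plan's threshold is 0.01. The earlier-study gap may also differ among players who go on to be concussed. These points weaken the error rates but not the offset itself.

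**The sex evidence is thin.** The pupillary statement mainly sets adolescents against adults, rests on data described as initial, and has no effect size. A quantified sex bias cannot be claimed.

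**Conclusion.** The point holds conditionally. If the peak or the AUC is chosen as the summary, and is computed on observed values as the text reads, a pre-injury gap passes in full into what is reported as recovery. For SEn by concussion history the article's own figures put this at 0.11 units on the peak and about 40 unit-days on the AUC. The standardised AUC difference is about 0.57 at an assumed correlation of 0.7 (0.54 to 0.59 for 0.8 to 0.6). For pupillary outcomes by sex the direction of concern is supported but the size is unknown. The article gives no figure for a pre-injury gap in PCSS or PFAB-TBI.

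With about 20 concussed players, the bias in the reported estimate matters more than false significance. Under an assumed Mann-Whitney test, the false-positive rate at p<0.01 is about 5% at correlation 0.7 with an even split, and 3 to 7% over correlations 0.5 to 0.9 and both splits examined.

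It would be tempting to conclude that the study will report spurious sex and history effects on recovery. The documents do not support that: the time to return to baseline may be chosen instead, not every outcome is shown to differ before injury, and the formal recovery models are already baseline-referenced.

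**What to change.** In the Statistical analysis section, define both summaries relative to the player's own preseason value: AUC as the trapezium area of visit value minus baseline, and peak as the largest change from baseline in the direction of impairment. Make the between-group curve comparison on the same scale. Curves of observed values can remain as a descriptive figure.

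No new assessments are needed, because the Abstract places the questionnaires, Y Balance and pupillary tests at preseason. The article should confirm that this includes PFAB-TBI, which its baseline comparison does not list although the recovery definition implies a baseline value.

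There are two costs. A direction of impairment must be named for each pupillary metric, for SEn and for reach distance; the article does not set these for every metric. Error in the single baseline measurement also enters every change score, so precision improves only where the within-player correlation exceeds about 0.5.

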**Trial registration number:**

ACTRN12622000931774p.

Strengths and limitations of this studyFemale adolescent rugby players have been overlooked in adolescent concussion research, this study seeks to address this with a large sample of both male and female adolescent rugby players.Many studies cease follow-up within 6 weeks postconcussion, this study adopts a prospective design which aims to track recovery of sport-related concussion for 12 months.This study uses innovative, portable and relatively low-cost technology, which may be feasible for use in a non-professional, youth sporting environment.Despite the growing popularity of female rugby in Northern Ireland, there is a limited population of female adolescent rugby players, in particular aged 16–18 years, to recruit from.Access to players at key follow-up dates may be challenging given the limited access to adolescent rugby players during school hours at an important examination stage for this population.

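### The area under the curve is an unscaled sum, so if it is the chosen summary, a player whose series ends early gets a smaller value for that reason alone

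*Protocol article*

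**What the plan says.** The Statistical analysis section of the protocol article plans one summary per concussed player and outcome, "based on either the peak value, the time to return to baseline or the area under the curve". Only the AUC is given a formula: the trapezium rule, carried out "by adding the areas under the graph between each pair of consecutive observations". The next step is stated as follows: "The most suitable summary measure will be used in the calculation of a median score (IQRs) for each outcome variable". Curves are also to be compared by sex and by concussion history.

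The same section sets the visits at "72 hours, 7 days, 14 days, 23 days, 90 days, 180 days and 365 days postconcussion". Shortened series are foreseeable. The Sample size section "allows for a 20% loss to follow-up over the entire study", and the list of strengths and limitations warns: "Access to players at key follow-up dates may be challenging given the limited access to adolescent rugby players during school hours".

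**The concern.** A sum over the pairs of visits a player has grows with every further visit attended. It is not divided by the days covered, and it is not cut at a date common to all players. Two players with the same values but different last visits therefore get AUCs on different scales, and the text contains nothing to keep them out of the same median.

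The effect is strongest for measures that are well above zero in healthy players, such as SEn, reach distance and pupil diameter, because their raw AUC is close to level multiplied by days observed. The last two intervals, day 90 to 180 and day 180 to 365, make up 275 of the 362 days, so the visits furthest from injury carry most of the total. At stake are the reported median and IQR, and the sex and history comparisons if one group loses more players than the other.

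**Working it through.** **The plan's own figure.** Sample size gives 250 enrolled, 20% loss and 10% concussed: 250 × (1 − 0.20) × 0.10 = 20. This reproduces the stated figure of about 20 players with recovery data. Before loss the same rates give 250 × 0.10 = 25 concussions, so about 5 of 25 could have a shortened series if partial data were analysed.

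**Formula.** AUC = Σ (tᵢ₊₁ − tᵢ) × (yᵢ + yᵢ₊₁)/2, with t = 3, 7, 14, 23, 90, 180, 365 days from the Statistical analysis section. At a constant level c this reduces to c × (last day − 3).

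| Last visit | Days covered | Share of 362 | Level needed to equal a completer's AUC |
|---|---|---|---|
| Day 7 | 4 | 1.1% | 90.5 times |
| Day 14 | 11 | 3.0% | 32.9 times |
| Day 23 | 20 | 5.5% | 18.1 times |
| Day 90 | 87 | 24.0% | 4.2 times |
| Day 180 | 177 | 48.9% | 2.05 times |

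The Outcome measures section gives day 21 where Statistical analysis gives day 23. With day 21 the share is 18/362 = 5.0%, which changes nothing of substance.

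**Ranking.** The documents give no recovery curves, so these PCSS series are assumed.

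- Never improves, constant at 40, last seen at day 23: 40 × 20 = 800. If complete: 40 × 362 = 14,480.
- Good recoverer (30, 20, 10, 5, 5, 5, 5), all visits: 100 + 105 + 67.5 + 335 + 450 + 925 = 1,982.5.

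On the raw sum, the player who never improved (800) ranks ahead of the good recoverer (1,982.5). Over a common window to day 23 the values are 800 and 272.5, and the order is right.

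**Time-averaging.** Dividing by days observed gives 800/20 = 40.0 and 1,982.5/362 = 5.5 per day, also in the right order. But an assumed slow recoverer (40, 35, 30, 25, 20, 15, 10) scores 625/20 = 31.3 per day if cut at day 23 and 6,020/362 = 16.6 if complete. On a falling curve, time-averaging overstates the early leaver.

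**Missed visits inside a series.** If the slow recoverer misses day 90, the trapezium bridges the gap: 6,077.5 against 6,020. Only a series that ends early, or starts late, loses area.

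**Group comparison.** Assumed: 10 v 10 players with identical distributions, constant levels with mean 1.0 (assumed) and SD 0.22 (the SEn figure in Sample size), and 4 of the 20 last seen at day 180. With all four in one group, that group's median AUC is about 19% lower. With a 1 v 3 split, the group with three is about 9% lower.

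**The case against.** The strongest reply is that the wording is only a textbook gloss on the trapezium rule, and that handling of incomplete series belongs in a full protocol or analysis plan not shown here. The second half is fair as far as it goes: the absence of a missing-data rule is not the point. The point is that the article itself fixes an unscaled sum, and that sum, applied as written to partial series, gives values that cannot be compared.

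Three further replies stand and limit the point.

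- AUC is one of three candidates. For outcomes where it would merely track follow-up time, the investigators may choose another measure.
- The figure of about 20 is already net of the 20% loss and may mean completers only. That 20% covers the whole cohort, including players lost before any concussion, so it is not a rate of shortened post-concussion curves.
- The warning about access concerns key dates. It supports the point only where a missed visit is at the end or the start of a series.

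A reader might infer that the rule inflates false positives. In the example above, a t-test at p<0.01 does reject in roughly 9 to 10% of simulated trials when all four dropouts are in one group. If four dropouts fall at random among 10 v 10, that split occurs with probability 2 × 210/4,845 = 8.7%. At 1 v 3 the rejection rate is about 0.5%, and averaged over random splits it is about 1.1%. The documents give no evidence that dropout depends on group, and they name the t-test only for baseline comparisons. The inflation reading is not supported.

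A reader might also infer that dropout always looks like good recovery. That holds only where higher is worse: PCSS, PFAB-TBI and SEn. For reach distance the early leaver looks worse.

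**Conclusion.** The point holds conditionally. Where AUC is the summary used and players with shortened series are included, the stated sum puts them on a smaller scale: 49%, 24% or 5.5% of a completer's AUC at the same level, for a last visit at day 180, 90 or 23. These shares follow from the visit days alone. The distortion of the median and IQR does not need unequal dropout; the bias in sex or history comparisons does. The 9% and 19% median shifts rest on the assumed splits and levels and are illustrations, not forecasts. With about 20 concussed players, a few shortened series are enough to matter.

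**What to change.** Add one sentence to the Statistical analysis section: where AUC is used, it is calculated over one pre-specified window common to all players compared, preferably on change from the preseason baseline, and the number of players contributing is reported by last visit. Raw AUCs with different end dates should not be pooled. Working with change from baseline means a player who is back at baseline adds no area, so the total no longer tracks attendance for that player. It does not replace the common window for players who have not recovered.

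A time-averaged AUC may be shown as a sensitivity analysis, with the note that it overstates early leavers when values fall over time.

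No new data are needed. The price is a choice of window. One ending at day 90, for example, leaves 275 of the 362 days out of this summary, while one ending at day 365 leaves out every player not seen then.

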#### Self-report questionnaires

The Post-Concussion Symptom Scale (PCSS) consists of 22 questions that relate to postconcussive symptoms. Users are asked to rate each symptom according to a 7-point Likert Scale ranging from 0 to 6. Higher scores indicate a higher severity of postconcussive symptoms. The greatest possible score is 132 and the lowest possible score is 0. The scale has a high internal consistency^41^ in healthy and concussed adolescents, its construct validity has been established^42^ and it can accurately discriminate between concussed and non-concussed athletes.^41^

The Paediatric Fear Avoidance Behaviour after Traumatic Brain Injury Questionnaire (PFAB-TBI) is a 16-item measure designed to assess fear avoidance following paediatric concussion developed based on FAB-TBI. The FAB-TBI was developed to assess fear-avoidance behaviour postconcussion in adults. Items are related to avoidance of activities (eg, work) due to fear of symptom consequences or symptom exacerbation (eg, worsened headache). For the PFAB-TBI self-report item content will remain the same with the exception of two items. Item 4 will be changed from ‘My work might harm my brain’ to ‘My schoolwork might hurt my brain’, and item 5 will be changed from ‘I should not do my normal work with my present symptoms’ to ‘I should not do my normal schoolwork with my present symptoms’. The PFAB-TBI asks respondents to rate agreement on statements related to avoidance behaviour over the past month from 0 (strongly disagree) to 3 (strongly agree). A total sum score will be used in the current study, where higher scores indicate greater fear-avoidance behaviour (possible range 0–48). Change scores will be calculated across testing dates.^30^

The Generalised Anxiety Disorder (GAD-7) is a 7-item questionnaire that has questions about possible problems the respondent may have been bothered by over the previous 2 weeks. Each question has four possible responses from ‘not at all’ to ‘nearly every day’ and scored 0–3, respectively. The GAD-7 has reported good reliability, as well as criterion, construct, factorial and procedural validity.^43^

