In an exploratory analysis, we will use logistic regression to examine the association between demographic variables (age, sex, previous injury) and recovery at 23-day follow-up. We will run separate models for each outcome measure (PCSS, Y Balance, PLRM, PFAB-TBI). Our previous research^4^ found that 90% of adolescent rugby players return to sport at 23 days postconcussion; this is also the minimal convalesce for adolescent players postconcussion based on Irish Rugby Football Union and World Rugby guidance, which are built around the latest medical research and expert-based opinion.^46^ Full recovery will be defined as a return to baseline (preseason) values for each respective outcome. Initially, we will conduct a series of univariate analyses to determine whether any predictor variables are associated with recovery. Correlations among predictor variables will be calculated to screen for any strong colinearity (r>0.8). Predictors demonstrating a p value less than 0.10 on univariate testing will be entered into a multiple logistic regression analysis. The strength of the predictive model will be determined using R^2^, p values and ORs, with 95% CIs.

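### The exploratory day-23 models reduce four scale measures to recovered yes/no for logistic regression on about 20 players, which discards at least a third of the information and may leave odds ratios inestimable

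*Protocol article*

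**What the plan says.** The last paragraph of Statistical analysis in the Protocol article, introduced as exploratory, states that "we will use logistic regression to examine the association between demographic variables (age, sex, previous injury) and recovery at 23-day follow-up". It adds: "We will run separate models for each outcome measure (PCSS, Y Balance, PLRM, PFAB-TBI"). The binary response is fixed by the sentence "Full recovery will be defined as a return to baseline (preseason) values for each respective outcome". Predictors are tested singly. Those with p below 0.10 go into a multiple logistic model, reported by R², p values and odds ratios with 95% CIs. Two reasons are given for day 23: 90% of players in the group's earlier work were back in sport by then, and it is the minimum convalescence period in the governing bodies' guidance.

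All four outcomes are scale measures with a preseason value for the same player. For PCSS, "The greatest possible score is 132 and the lowest possible score is 0". PFAB-TBI runs from 0 to 48. The Y Balance measures (normalised reach, sample entropy) and the pupillary diameters, velocities and times are continuous.

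On numbers, Sample size says: "This will generate recovery data from approximately 20 participants presenting with a new concussion". No effect size, recovery share or power is given for the day-23 models. Earlier in Statistical analysis, the significance threshold is set at 0.01 for all tests. The serial data are to be summarised by peak, time to return to baseline or area under the curve, and compared by sex and concussion history.

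**The concern.** Cutting a score at the baseline value discards how far each player is from it. A player 1 point above the preseason PCSS and a player 60 points above it both count as not recovered. The two reasons given support the choice of day; neither requires the cut.

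With about 20 players there is little information to spare. The odds ratio also needs both recovered and non-recovered players within each category of a binary predictor. If nearly everyone has recovered, or nearly no one has, that will often fail.

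What is at stake is the only stated regression of recovery on age, sex and previous injury. The Discussion places the effect of concussion history, sex and age on recovery within the primary aim.

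**Working it through.** **1. The plan's own figure.** The enrolment target is 250, and Sample size explains it as follows: "This figure allows for a 20% loss to follow-up over the entire study and assumes a 10% concussion prevalence over a single playing season". So 250 × (1 − 0.20) × 0.10 = 20 concussed players, which reproduces the stated number. Recruitment is split 125 males to 125 females, so 10 v 10 among the concussed is taken as the working case.

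**2. Assumptions not in the article.** Change from baseline at day 23 is normal with equal SD. Tests are two-sided (sidedness is not stated). The share back to baseline is not given, so 50%, 70% and 90% are shown. The 90% borrows the return-to-sport figure, which is not the same quantity.

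**3. Information lost.** For a normal score cut so that a share p falls on one side, with z the normal quantile of p, the large-sample efficiency of the binary analysis is φ(z)² / [p(1 − p)].
- p = 50%: 0.399² / 0.25 = 0.637, a loss of 36%
- p = 70%: 0.348² / 0.21 = 0.576, a loss of 42%
- p = 90%: 0.1755² / 0.09 = 0.342, a loss of 66%

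The even split is the best case, so the loss is at least about a third.

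**4. Power at a sex difference of 1.0 SD, 10 v 10.** The full-scale test is a two-sample t-test with 18 df and noncentrality 1.0 × √(10/2) = 2.24. For the cut outcome, the recovery probabilities in the two sexes are 69% v 31%, 86% v 54% and 97% v 83% for overall shares of 50%, 70% and 90%. The logistic likelihood-ratio test of sex is applied to these. Entries are simulated power, with exact enumeration of all 11 × 11 possible counts in brackets.

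| Two-sided level | Full scale | Cut, 50% recovered | Cut, 70% | Cut, 90% |
|---|---|---|---|---|
| 5% | 56% (56.2) | 41% (41.2) | 43% (43.6) | 20% (19.2) |
| 1% (plan's threshold) | 29% (29.4) | 22% (21.9) | 17% (17.3) | 1% (1.4) |
| 10% (plan's screen) | 69% (69.4) | 57% (57.6) | 50% (50.7) | 43% (42.2) |

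At 5% the loss is about 15, 13 and 36 points; at 1% it is about 7, 12 and 28.

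**5. Power at 0.5 SD.** This is the only effect size in the article, given for the baseline comparison of concussion-history groups and not for recovery. The noncentrality is 0.5 × √5 = 1.12. Exact results:
- 5% level: 18.5% on the full scale against 14.3%, 17.4% and 9.4%, a loss of 4.2, 1.1 and 9.1 points.
- 1% level: 6.0% against 5.3%, 4.4% and 0.4%, a loss of 0.7, 1.6 and 5.6 points.

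**6. Can the odds ratio be estimated?** With 90% recovered, about 20 × 0.10 = 2 players are not recovered. The chance that at least one sex is all or none recovered is:
- No sex effect: 0.9¹⁰ = 0.349, and the chance of none recovered is negligible. So 1 − (1 − 0.349)² = 0.576, about 58%.
- 1.0 SD effect (97.4% v 82.6%): 0.974¹⁰ = 0.768 and 0.826¹⁰ = 0.148. So 1 − 0.232 × 0.852 = 0.80, or 80%.

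In those datasets the ordinary maximum-likelihood odds ratio for sex is zero, infinite or undefined, and the usual 95% CI carries no meaning.

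**The case against.** **The analysis is exploratory, and full-scale analysis exists elsewhere.** Both are true. Peak and area under the curve keep the size of the deficit and are to be compared by sex, the predictor used in the worked example, and by concussion history. A reader might infer that the plan never analyses recovery on the original scale; the article does not support that. What remains is narrower. No scale-based analysis by age is stated. One of the three candidate summaries, time to return to baseline, uses the same threshold. The logistic models are still the only stated regression on the predictors.

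**The loss depends on the effect size.** This stands. A reader might infer from the 1.0 SD row at an even split that the cut always costs 14 points or more. It costs about 13 at 70% recovered and 5%, about 7 at 50% recovered and 1%, and only 1 to 9 points at 0.5 SD. At 0.5 SD the limit is the 20 players, which no change of model cures.

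**The tests compared do not have equal false-positive rates.** Correct. With no difference, the likelihood-ratio test rejects 7.7% at a nominal 5% (70% recovered) and 18.5% at the 10% screen (90% recovered). This flatters the logistic test in those cells, so matching the rates would widen the gap there. The point differences are still approximate.

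**Yes/no recovery answers its own question, and PCSS and PFAB-TBI are likely to be skewed.** A mean difference does not say who is back to baseline. The planned number and percentage returned to baseline at each visit do say that. The power figures rest on normality, so the gain is not shown for the two questionnaires.

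**Conclusion.** The point holds as a minor improvement to an exploratory analysis. The cut is not needed for the stated reasons and discards at least about a third of the information under normality, two thirds if 90% recover. In power terms it ranges from about 1 point at 0.5 SD to about 36 points at 1.0 SD with 90% recovered (5% level). If recovery is as common as return to sport, the planned odds ratio for sex would have no finite estimate in more than half of datasets. All of this assumes 10 v 10, normal change scores and two-sided tests, and the recovery share is unknown.

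A reader might also infer that a null logistic result would be reported as showing no effect of sex or age. The article does not say so: it commits to confidence intervals, which would show the imprecision wherever they can be computed.

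**What to change.** In the exploratory paragraph of Statistical analysis, replace the logistic models with a regression, for each outcome, of the day-23 value on the preseason value plus one predictor at a time (age, sex, previous injury). Report the adjusted difference or slope with its 95% CI. For PCSS and PFAB-TBI, which are likely to be skewed, use a log transformation that allows for zeros, or a rank-based or ordinal model. Keep the number (%) returned to baseline at each visit as a description.

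The cost is wording only: no new data, visits or players. The downside is that the result is a difference in score and not an odds ratio of recovery. The change does not make 20 players adequate; intervals will still be wide and should be reported as such.
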